## Methodology

### Study aims

The primary aim of this study is to compare absolute weight change among participants receiving daily healthy meals or produce box versus matched controls (standard of care) at 16 weeks from baseline:This aim tests the hypothesis that receiving daily healthy meals will result in greater absolute weight loss compared to receiving a produce box or standard of care at 16 weeks from baseline.This aim tests the hypothesis that receiving either daily healthy meals or a produce box will result in greater absolute weight loss compared to standard of care at 16 weeks from baseline.
The secondary aim of this study is exploratory and will compare daily healthy meals or produce box versus matched controls in improving chronic disease markers:This aim tests the hypothesis that receiving daily healthy meals will result in greater improvement in hbA1c and blood pressure compared to receiving a produce box or standard of care box at 16 weeks, six months, and 12 months from baseline.This aim tests the hypothesis that receiving either daily healthy meals or a produce box will result in greater improvement in weight, hbA1c and blood pressure compared to standard of care at 16 weeks, six months, and 12 months from baseline.
To assess whether receiving daily healthy meals or a produce box in conjunction with nutrition counseling and education results in improvement in food insecurity, diet quality, depression, self-efficacy for healthy eating and healthy weight, and self-efficacy for chronic disease management from baseline to 16 weeks.

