### Study design

This study is a parallel-arm quasi-randomized control trial with nonequivalent matched controls, which will be conducted between January 2022 and December 2023. Seventy adult patients recruited from our ambulatory practice will be randomly assigned to receive either: i) daily healthy frozen meals or ii) a weekly produce box and recipes for 15 weeks. Each study arm will comprise 35 patients with a documented diagnosis of obesity (body mass index [BMI] equal to or greater than 30kg/m^2^) and one or more of the following conditions: pre-type 2 diabetes/type 2 diabetes or hypertension. Participants will complete an in-person baseline visit and a follow-up visit at 16 weeks from baseline, and their medical charts will be reviewed for trends in these biomarkers at six months and 12 months from baseline. Healthy meals or a produce box will be shipped to the home address of participants once a week. Healthy meals provided in the study are low-sodium and diabetic-friendly ready-to-heat and serve breakfast, lunch, and dinner items. The produce box provided in the study will comprise fresh vegetables and fruits. For participants receiving a produce box, recipes utilizing items contained in the box will be available at the vendor’s website.

All participants will complete one individual medical nutrition therapy session via phone with a dietitian. The individual medical nutrition therapy appointment will occur within two weeks of enrollment in the study. A total of four nutrition and health videos, each under 10 minutes in length, will be available for participants to view between weeks 3 and 15 of the study. The complete study procedures are outlined in Table 1. Participants will be required to view the videos on healthy eating and weight loss and, as applicable to their health status, videos on type 2 diabetes and hypertension (see Table 2). The Healthie application (https://www.gethealthie.com/?afmc=a46i) will be utilized for nutrition education programming. Through the Healthie application, participants will receive automated text and/or email reminders to view educational videos. This feature is designed to drive compliance and completion of the nutrition education component. A report will be generated to provide completion percentage and other details based on participant engagement. The Healthie application is compliant with the US Health Insurance Portability and Accountability Act.

**Table 1. tbl1:** Schedule of study activities

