Study activity	Baseline visit (W0)	Week 2 (W0–W2)	Week 3 – 15 (W3–W15)	Week 16 visit (W16 ± 7 days)	6 months	12 months
Informed consent process	x					
Anthropometric data (weight, height, and blood pressure)	x			x	x	x
HbA1c	x			x	x	x
Completion of study questionnaires	x			x		
Individual nutrition counseling session		x				
Nutrition education videos			x			

**Table 2. tbl2:** Expected viewership of nutrition education videos

	Video title			
	Introduction to nutrition	Nutrition and weight loss	Nutrition and diabetes	Nutrition and hypertension
All participants	x	x		
Participants with pre-/type 2 diabetes			x	
Participants with hypertension				x
Participants with pre-/type 2 diabetes AND hypertension			x	

The control group will comprise 70 participants matched to intervention group participants based on BMI, diagnosis of pre-type 2 diabetes/type 2 diabetes, and/or hypertension. Control group participants will be identified from the electronic medical record, Epic^®^, after enrollment of all intervention arm participants has been completed. A flow chart of participant recruitment and completion of study activities is shown in Figure 1. Our study protocol adheres to the SPIRIT guidelines for clinical trial protocols (Chan *et al.*, 2013) and is registered on ClinicalTrials.gov with identifier NCT05174078.

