### Study population

Current patients at our ambulatory practice who are 18 years and older, and are of any gender and race, are eligible for enrollment in the study. Patients who have food allergies, are pregnant or planning to become pregnant, have no access to internet, or require English language interpretation will be excluded from participation. Additional exclusion criteria are participation in nutrition counseling with our partnering organization within the past six months, current participation in a structured weight loss program, or current use of weight loss medications. Medications prescribed for other conditions but that may have a weight loss effect, for example, metformin or GLP-1 agonists prescribed for diabetes treatment or topiramate prescribed for migraine headaches, will not result in the exclusion of potential participants.

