### Randomization

Randomization of participants will be conducted using the central randomization module available in the Research Electronic Data Capture (REDCap) program, a secure online database that will be utilized for data collection and management (Harris *et al.*, 2009, 2019). Randomization and allocation will occur in blocks of four. The allocation sequence was generated for a total of 80 participants using randomization software in the Sealed Envelope website (https://www.sealedenvelope.com/simple-randomiser/v1/lists) and uploaded into our study’s REDCap database. Following consent into the study and collection of all baseline data, study participants will be randomly allocated to the healthy meals or produce box group in a 1:1 ratio using the randomization sequence pre-entered into REDCap.

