### Data analysis

The independent variables in this study are study arm (healthy meals, produce box, and matched controls [standard of care]), nutrition counseling and education, and time (pre-intervention, 16 weeks, six months and 12 months). The primary dependent variable (outcome) is absolute weight change at 16 weeks between groups. The secondary dependent variables (outcomes) are as follows: i) absolute weight change at six months and 12 months from baseline; ii) change in hbA1c, dosage, and number of diabetes medications; iii) change in dosage and number of blood pressure medications, and; iv) change in numeric rating from baseline to 16 weeks for food insecurity, diet quality, depression as well as self-efficacy for health eating, healthy weight, and chronic disease management. A final outcome of interest is satisfaction rating for the interventions provided in the study, measured using a non-validated questionnaire developed for this study.

Descriptive statistics will be calculated for demographic data and for each dependent variable by group, nutrition counseling and education, and time. Separate repeated-measures ANOVAs will be conducted for each dependent variable with the between subjects factor group (healthy meals, produce box, and matched controls) and the within subjects factor time (pre-intervention and 16 weeks). *Post hoc* testing will be conducted as appropriate. Effect sizes will be calculated between pre-intervention and 16 weeks to capture the changes from pre- to post-intervention. Missing data will be analyzed using an intention-to-treat strategy. Statistical analysis will be performed by a biostatistician using SAS statistical software. The biostatistician will be blinded to the intervention for each group to eliminate potential bias during data analysis.

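### The primary analysis puts randomised food arms and non-randomised chart controls into one group factor, with no stated adjustment and no fixed contrast to keep the two comparisons apart

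*Protocol article*

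**What the plan says.** All references are to the protocol article.

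- **Study aims.** The primary aim reads: "compare absolute weight change among participants receiving daily healthy meals or produce box versus matched controls (standard of care) at 16 weeks from baseline". Both hypotheses under it involve standard of care; the first also names meals against produce box.
- **Randomization.** Only the two food arms are randomised: "study participants will be randomly allocated to the healthy meals or produce box group in a 1:1 ratio".
- **Study design.** The study is called a "parallel-arm quasi-randomized control trial with nonequivalent matched controls". On the controls: "The control group will comprise 70 participants matched to intervention group participants based on BMI, diagnosis of pre-type 2 diabetes/type 2 diabetes, and/or hypertension". On timing and source: "Control group participants will be identified from the electronic medical record, Epic^®^, after enrollment of all intervention arm participants has been completed".
- **Study population.** Some weight-active drugs are allowed: "metformin or GLP-1 agonists prescribed for diabetes treatment or topiramate prescribed for migraine headaches, will not result in the exclusion of potential participants".
- **Data analysis.** Each outcome gets a repeated-measures ANOVA with the "between subjects factor group (healthy meals, produce box, and matched controls") crossed with time (before the intervention and 16 weeks). Post hoc tests follow where appropriate, without a list of contrasts. No covariate, propensity method or matched-set term is named.
- **Strengths and limitations.** The lack of a parallel control group is listed as a limitation and the comparison with matched controls as the main strength. No analytic remedy for the non-randomised comparison is given.

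**The concern.** Two kinds of evidence answer the primary aim. Meals against produce is protected by randomisation. Either food arm against standard of care is not: food-arm patients respond to a flyer or an invitation and agree to take part, while controls are picked from records afterwards. A single three-level factor gives both the same standing, and its overall F test does not say which one drove a significant result.

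For the primary outcome the relevant term is group by time, which amounts to comparing weight change across groups. It cancels differences in starting level that stay constant. It does not cancel differences in how weight would have moved without the food. Such differences could come from readiness to lose weight, age, sex, use of weight-active drugs, or the fact that participants are weighed at a scheduled week-16 visit while control data come from retrospective chart review. At stake is the main claim of the study, that healthy food beats standard of care.

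**Working it through.** **Inputs.** From Sample size determination: means of 92 kg (controls), 78.4 kg (meals) and 85.2 kg (produce), SD 16 kg, alpha 0.05, power 0.80, 28 per group before attrition, 35 per food arm. From Study design: 70 controls. Assumed, because the article does not give them: the SD of weight change (5 and 8 kg) and the excess loss b of volunteers over controls with no food effect (1, 2 and 3 kg).

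**Step 1. Reproduce the plan's figure.** The noncentrality of a one-way ANOVA is λ = Σ nᵢ(μᵢ − μ̄)² / SD². With 28 per group, μ̄ = 85.2 and λ = 28 × (6.8² + 6.8² + 0²) / 16² = 10.11. Power is 80.5% (78.9% at 27), so the stated 28 per group is confirmed.

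**Step 2. Split λ into its randomised and non-randomised parts.** The mean of the two food arms is (78.4 + 85.2)/2 = 81.8, which is 10.2 kg below controls.
- Randomised part: 6.8² / [16² × (1/n_meals + 1/n_produce)]
- Non-randomised part: 10.2² / [16² × (1/n_controls + 1/n_food)]

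| Group sizes (controls/meals/produce) | Randomised | Non-randomised | Total | Non-randomised share |
|---|---|---|---|---|
| 28/28/28 | 2.53 | 7.59 | 10.11 | 75% |
| 70/35/35 | 3.16 | 14.22 | 17.39 | 82% |

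The SD cancels from the share, so the share depends only on the planned means and group sizes.

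**Step 3. Power of the randomised contrast alone.** The difference is 6.8 kg, SD 16, two-sided 0.05. At 35 per arm the noncentral t parameter is 6.8 / (16 × √(2/35)) = 1.78, and power is about 42%. At 28 per arm it is about 35%. The normal approximation gives 87 per arm for 80% power. The 16 kg is the SD of body weight; if the SD of change is smaller, power is higher.

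**Step 4. Rejection rate with no food effect.** With two time points, the group-by-time F test equals a one-way ANOVA on change. Take mean changes of 0, −b and −b at 70/35/35, so λ = b² / [SD² × (1/70 + 1/70)] = 35b²/SD². For b = 2 and SD = 5, λ = 35 × 4/25 = 5.6.

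| Excess loss b in volunteers | SD of change 5 kg | SD of change 8 kg |
|---|---|---|
| 1 kg | 17% | 9% |
| 2 kg | 54% | 24% |
| 3 kg | 89% | 49% |

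The nominal rate is 5%. No attrition is applied. The table illustrates sensitivity; it does not estimate the bias in this trial.

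**The case against.** The case for the plan has real weight.

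- **The design is disclosed.** The article calls the controls nonequivalent and lists the missing parallel control group as a limitation, with reasons of funding and ethics. This stands: the point concerns the analysis, not concealment.
- **The model handles part of the problem.** The within-subject factor removes stable level differences, so not matching on weight in kilograms matters less than it first appears. This stands; trajectory differences remain.
- **Post hoc tests could extract meals against produce, and the first hypothesis names it.** This stands in part. The contrast can be obtained, but it is not fixed in advance or set apart as the randomised one.
- **The article is condensed.** A reader might infer that further matching variables were rejected, or that the exclusions (structured weight-loss programme, weight-loss drugs, pregnancy) do not apply to controls. The documents do not support that: they are silent, and say that controls come from the same patient population. The model, however, is stated, and as stated it has one pooled group factor.
- **The biases do not all favour the food arms.** Motivation among volunteers would inflate the apparent benefit. Weight-loss programmes or drugs among controls would shrink it.

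A reader might also try to size the bias from GLP-1 agonist use: a 10 to 20 point imbalance times 3 to 5 kg per user gives 0.3 to 1.0 kg. Those inputs have no source in the article. The result is at most 1.0/6.8 = 15% of the planned produce effect, and matching on diabetes diagnosis should limit the imbalance. It does not carry the point.

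**Conclusion.** The point holds in a limited form and should be fixed. The comparison with standard of care is open to confounding of weight trajectory that the stated analysis does not address, and the stated test does not separate it from the randomised comparison. A reader might infer that the comparison is confounded in a known direction or by a known amount; nothing in the article shows that.

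On the plan's own means, the observational contrast supplies 75% of the omnibus noncentrality at 28 per group and 82% at 70/35/35, so a significant F would mainly be observational evidence. Under the assumed 1 to 3 kg excess loss in volunteers, the F test would reject 17% to 89% of the time (SD of change 5 kg) or 9% to 49% (8 kg) with no food effect. These rates rest on assumed values; the shares do not.

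**What to change.** 1. Prespecify meals against produce as a separate, randomised contrast, and report its power on the plan's own inputs (about 42% at 35 per arm).
2. Analyse the food arms against controls as an observational comparison of weight change. Adjust for baseline weight, age, sex, diabetes and hypertension status and baseline use of weight-active drugs, and account for matched sets.
3. Apply to control selection those Study population criteria that a chart can show. Give each control an index date and a 16-week weight window aligned with the participants'.
4. Word conclusions against standard of care as association. Adjustment cannot remove the effect of volunteering, so this is needed even after steps 2 and 3.

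**Cost.** A few more chart fields for 70 controls, one more model and a smaller pool of eligible controls. Some criteria, such as internet access or planning a pregnancy, may not be recoverable from the record. The low power of the randomised contrast becomes openly visible; it is already implied by the present inputs.

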**Methods::**

This parallel-arm quasi-randomized control trial will be conducted between January 2022 and December 2023. Seventy adult patients recruited from a single academic medical center will be randomly assigned to receive either: i) daily ready-made frozen healthy meals or ii) a weekly produce box and recipes for 15 weeks. Participants will, additionally, take part in one individual nutrition therapy session and watch videos on healthy eating, weight loss, type 2 diabetes, and hypertension. Data on weight, height, glycated hemoglobin, blood pressure, and diabetes and blood pressure medications will be collected in-person at the baseline visit and at 16 weeks from baseline and via medical chart review at six months and 12 months from enrollment. The primary outcome of the study is weight loss at 16 weeks from baseline. Pre- and post-intervention survey data will be analyzed for changes in food insecurity, diet quality, depression, as well as self-efficacy for health eating, healthy weight, and chronic disease management. Through retrospective chart review, patients who received standard of care will be matched to intervention group participants as controls based on body mass index, type 2 diabetes, and/or hypertension.

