## Data collection

### Demographic and clinical data

Participants’ date of birth, sex, race, and ethnicity will be collected as part of demographic data. Objective health data that will be collected are weight, height, hbA1c, blood pressure, prediabetes/diabetes diagnosis and classification, hypertension diagnosis and classification, diabetes and blood pressure medications, and comorbid chronic conditions. These data will be collected in-person at the baseline visit and at 16 weeks from baseline and via chart review of routine care at six and 12 months from enrollment in the study.

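### The control-matching rule pools prediabetes with type 2 diabetes and does not clearly require agreement on hypertension as well, which leaves comparisons with controls on HbA1c and diabetes medication open to confounding

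*Protocol article*

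**What the plan says.** The Study design section says that controls are matched on BMI and "diagnosis of pre-type 2 diabetes/type 2 diabetes, and/or hypertension". The Abstract (Methods) describes patients "matched to intervention group participants as controls based on body mass index, type 2 diabetes, and/or hypertension", with no mention of prediabetes.

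Eligibility, also under Study design, requires obesity plus "one or more of the following conditions: pre-type 2 diabetes/type 2 diabetes or hypertension". Table 2 likewise assigns the diabetes video to pre-/type 2 diabetes as a single group of participants.

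Study population states that "metformin or GLP-1 agonists prescribed for diabetes treatment or topiramate prescribed for migraine headaches, will not result in the exclusion of potential participants", and gives these drugs as examples of medication that may have a weight loss effect. Medication is not among the matching factors.

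Demographic and clinical data lists "prediabetes/diabetes diagnosis and classification, hypertension diagnosis and classification" among the data collected, together with diabetes and blood pressure medications.

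On outcomes, Study aims hypothesizes "greater improvement in weight, hbA1c and blood pressure compared to standard of care" for either intervention, within a secondary aim labelled exploratory. Data analysis lists "change in hbA1c, dosage, and number of diabetes medications" as a secondary outcome. The only factors named for the repeated-measures ANOVA are group and time.

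**The concern.** Controls are not randomized. They are drawn from the medical record after enrollment of the intervention arms is complete, so matching is the main stated protection for every comparison with standard of care. HbA1c change and change in diabetes drugs depend strongly on whether a patient has prediabetes or type 2 diabetes and on what treatment is already in place. If the matching rule does not tell these classes apart, the groups can differ in their mix of classes, and the outcomes can then differ for reasons unrelated to the food.

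The weight comparison with controls, which is part of the primary aim, could also be touched. Patients taking diabetes drugs that may affect weight remain eligible, and diabetes class is the nearest available stand-in for that treatment among the diagnoses used for matching. Pooling the classes discards it.

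**Working it through.** The plan gives no figure on this point, so the check compares the wordings and lists which pairs each one allows.

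**Step 1. Eligible cells.** Glycemic status has three levels (none, prediabetes, type 2 diabetes) and hypertension has two: 3 x 2 = 6 cells. The cell with neither condition is ineligible, which leaves 5.

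**Step 2. Cells from which a valid control may come.** The strict reading of Study design requires the same pooled glycemic status and the same hypertension status. The loose reading requires agreement on at least one condition.

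| Participant has | Strict reading | Loose reading | Three levels plus hypertension |
|---|---|---|---|
| Type 2 diabetes and hypertension | 2 of 5 | 5 of 5 | 1 of 5 |
| Type 2 diabetes only | 2 of 5 | 4 of 5 | 1 of 5 |
| Prediabetes and hypertension | 2 of 5 | 5 of 5 | 1 of 5 |
| Prediabetes only | 2 of 5 | 4 of 5 | 1 of 5 |
| Hypertension only | 1 of 5 | 3 of 5 | 1 of 5 |

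Even on the strict reading, every participant with a glycemic diagnosis may be paired across classes. Pairing someone who has both conditions with a control who shares only hypertension is possible on the loose reading alone.

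**Step 3. The Abstract's rule.** Taken literally, a participant eligible through prediabetes alone has no diagnosis to be matched on, and BMI is the only remaining factor. The two statements therefore give different matches for that participant.

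**Step 4. What the stated model removes.** Write HbA1c at baseline as a_g for group g and at 16 weeks as a_g + c_g. The group-by-time contrast between an intervention group and controls is c_intervention - c_control. A constant baseline gap in a_g cancels. A difference in the usual-care change c_g does not cancel, and with only group and time named in the model nothing else addresses it.

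**Step 5. Illustration, all inputs assumed.** Let p be the difference between groups in the share with type 2 diabetes among those with a glycemic diagnosis, and d the difference in usual-care HbA1c change between the classes over 16 weeks. The apparent group difference with no food effect is p x d.

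- p = 0.2 (60% versus 40%), d = 0.3 to 0.5: 0.2 x 0.3 = 0.06 and 0.2 x 0.5 = 0.10 points.
- p = 0.4 (80% versus 40%), d = 0.3 to 0.5: 0.4 x 0.3 = 0.12 and 0.4 x 0.5 = 0.20 points.
- p = 0: no difference.

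The sign reverses if the controls hold the larger share of type 2 diabetes. If patients with hypertension only are included in the HbA1c analysis, the figure shrinks in proportion. The documents supply neither p nor d.

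**The case against.** The strongest reply is that a journal article uses shorthand. The slash in the matching sentence also appears in "prediabetes/diabetes diagnosis and classification", where classes are evidently recorded, so it need not mean pooling. The and/or can be read as mirroring eligibility: match on whichever conditions the participant has. The Abstract may simply have shortened the term. Exact levels and calipers commonly sit in a fuller document that is not shown.

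Part of this stands. The hypertension-only pairing depends on one of two readings and cannot be asserted as the plan's intention. The absence of a BMI caliper is operational detail and is not held against the plan. The pooling is different: eligibility and Table 2 both treat prediabetes and type 2 diabetes as one group, and nothing in the matching sentence asks for the same class, so a cross-class pair meets the rule as written.

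A reader might infer three stronger points that the documents do not support.

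- **Eligibility is defective.** It is not. Admitting either condition is a legitimate choice, and the eligibility sentence does not use and/or.
- **The bias has a known size and favors the food.** No class shares or usual-care changes are given, no reason is stated why controls should have less type 2 diabetes, and no HbA1c cut-off is used for selection that would by itself predict regression to the mean.
- **Matching on class would equalize starting HbA1c and drugs.** It would not, since type 2 diabetes spans a range of both.

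The protocol also calls the controls nonequivalent and lists the lack of a parallel control group as a limitation. That is candid, but it does not settle the wording of the rule.

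**Conclusion.** The concern holds for the matching rule. As written, the rule accepts a pair with type 2 diabetes on one side and prediabetes on the other. It does not clearly require agreement on both glycemic status and hypertension, and it is stated differently in the Abstract. The consequence is confounding of unknown direction and size in the comparisons with controls on HbA1c and diabetes medication, which the protocol labels exploratory. An effect on the primary weight comparison with controls is possible through unmatched diabetes drugs, but cannot be shown from the documents. The comparison between the two randomized arms does not use the controls and is untouched.

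The range of 0.06 to 0.20 HbA1c points, in either direction, rests entirely on the assumed inputs shown and serves only to indicate scale. The change is worth making because it is cheap, not because a large bias has been demonstrated.

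**What to change.** State one matching rule, in the same words, in the Abstract and under Study design. Match on glycemic status in three levels (none, prediabetes, type 2 diabetes) and on hypertension (yes/no), as two separate required factors alongside BMI, and drop the and/or.

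Because class does not fix starting HbA1c or treatment, adjust the HbA1c comparison with controls for baseline HbA1c and baseline diabetes medication. Both are already collected for participants; for controls they would have to come from the chart, and their completeness there is not documented.

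The cost is a rewording before controls are drawn, plus two covariates. Five eligible cells in place of three pooled ones (2 x 2 = 4, less the cell with neither condition) will make some matches harder to find. Since controls are selected after enrollment is complete, the number needed in each cell will be known beforehand. If controls have already been drawn, report the balance by glycemic class and hypertension and adjust for both.
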